## Abstract

**Introduction:**

Patients with Parkinson’s Disease (PD) require an all-encompassing and individualized care including pharmacological as well as non-pharmacological treatment approaches, such as physical therapy, occupational therapy and speech and swallowing therapy. ParkinsonAKTIV is an innovative, multidisciplinary, and comprehensive approach to guide this non-pharmacological PD treatment in northwestern Germany. Its online communication platform called JamesAKTIV has been developed to enhance and standardize PD healthcare professionals’ communication. The implementation of ParkinsonAKTIV and JamesAKTIV is accompanied through a detailed process evaluation and to gather evidence on the impact on patient-related outcomes, such as health-related quality of life and healthcare costs for people with PD through an effectiveness evaluation.

**Methods:**

The study design contains two parts: (1) first, a quantitative effectiveness evaluation is conducted utilizing a prospective quasi-experimental approach with a control group which examines PD patient’s health-related quality of life and physician-assessed PD patient’s health status (Unified Parkinson Disease Rating Scale). Moreover, a health economic evaluation of the ParkinsonAKTIV intervention is conducted using patient-reported outcomes and cost data as well as routine data from a statutory health insurance. (2) Second, a mixed-methods process evaluation among healthcare professionals, which examines the feasibility and potential barriers and facilitators of ParkinsonAKTIV for routine care, is performed. Quantitative results from a social network analysis and a survey among healthcare professionals will be triangulated with data from qualitative stakeholder interviews and focus group discussions.

**Perspective:**

Findings are expected to provide evidence of an increase in quality of life of patients with PD, less severe PD symptoms, and a better ability to participate in activities of daily living. ParkinsonAKTIV has the potential of increasing PD patients’ quality of care through sufficient and more tailored prescription of non-pharmacological therapies. It is anticipated that ParkinsonAKTIV will improve communication among health professionals. Results from the ParkinsonAKTIV study will provide first practice-oriented evidence and a roadmap for implementation of an online tool for a comprehensive, multidisciplinary care PD network for patients and their caregivers in routine care in Germany.

*Trial registration* ClinicalTrials.gov: registration number NCT05251298 (retrospectively registered: https://clinicaltrials.gov/ct2/show/record/NCT05251298).

## Introduction

Parkinson’s disease (PD) is the second most common neurodegenerative disorder. Its course is generally slowly progressive and results in a variety of motor and non-motor symptoms [18]. In 2019, worldwide, approximately 8.5 million people have been affected by PD [16, 18]. Patients with PD (PwP) require a comprehensive and individualized management including medications, deep brain stimulation, and non-pharmacological treatments, such as physical therapy, occupational therapy as well as speech and swallowing therapy [4]. International network approaches have been shown to improve quality of life, reduce hospital admissions, and minimize the general burden of disease for PwP and their caregivers [11]. Notably, a study based on German routine data from a statutory health insurance revealed that there is a nationwide lack in non-pharmacological therapies for PwP [6]. Due to the fragmented German healthcare system with its inadequate collaboration and communication between healthcare professionals, an unmet need for comprehensive PD treatment approaches exists. Hence, an innovative treatment approach is needed to address and bridge these gaps in communication and collaboration through including a wide range of healthcare professionals, intimately involved in a community-care setting.

The *ParkinsonAKTIV* study, described in this paper, implements and evaluates such an innovative, multidisciplinary and comprehensive treatment approach for PwP in a region in northwestern Germany. As an essential part of the ParkinsonAKTIV study, an online communication platform to enhance PD healthcare professionals’ communication, called *JamesAKTIV*, is built and evaluated. The ParkinsonAKTIV study is set out to reach two aims: (1) first, to understand the implementation process and care process of ParkinsonAKTIV (and JamesAKTIV) through a detailed *process evaluation*. (2) Second, to gather evidence on the impact on patient-related outcomes, such as health-related quality of life and healthcare costs for PwP, through an *effectiveness evaluation*.

## Methods

### Study design

The present study follows a hybrid type 1 study design [19], focusing on implementation process factors and outcomes in the context of an effectiveness trial in a prospective quasi-experimental study with control group. A mixed-methods process evaluation among healthcare professionals examines the feasibility and potential barriers and facilitators of ParkinsonAKTIV for routine care, as well as the communication within the regional multidisciplinary Parkinson’s Network Muensterland (PNM+) consisting of medical and non-medical professionals involved in the treatment of patients with PD. For this purpose, quantitative results from a social network analysis and a survey among healthcare professionals will be triangulated with data from qualitative stakeholder interviews and focus group discussions.

Further, the quantitative effectiveness evaluation with two study arms (i.e., intervention arm and observational control arm) examines PD patient’s health-related quality of life and physician-assessed PD patient’s health status (e.g., with the Unified Parkinson Disease Rating Scale (UPDRS)). Moreover, a health economic evaluation of the ParkinsonAKTIV intervention is conducted using patient-reported outcomes and routine data from a German statutory health insurance.

The study observation period is set to 12 months, and data for the effectiveness evaluation and the associated health economic evaluation will be collected at five timepoints, as shown in Table 1.

**Table 1 Tab1:** Trial flow-chart according to SPIRIT guidelines with schedule of enrollment, intervention, and assessment

Timepoint	Study period					
	Preceding study	Enrolment/allocation	Post-allocation			Close-out
	− *t*_1 (12 months prior)_	0	*t*_1_	*t*_2_	*t*_3_	*t*_4 (12 months)_
*Enrolment*						
Eligibility screen		X				
Informed consent		X				
Allocation		X				
*Interventions*						
ParkinsonAKTIV						
Control Group (treatment as usual)						
*Assessments*						
Demographic aspects		X				
PDQ-39		X		X^a^		X
FIMA		X		X^a^		X
Schwab & England—activities of daily living scale		X^a^	X^a^	X^a^	X^a^	X^a^
UPDRS		X^a^	X^a^	X^a^	X^a^	X^a^
Hoehn & Yahr scale		X^a^	X^a^	X^a^	X^a^	X^a^
Routine data	X	X	X	X	X	X

PDQ-39 Assessment of patient-reported health-related quality of life with the Parkinson’s Disease Questionnaire. *FIMA* assessment of patient-reported healthcare costs. *UPDRS* assessment of patient’s PD-related status through neurologists

^a^Only assessed in the intervention group

This study is registered at ClinicalTrials.gov (registration number NCT05251298). Ethical approval has been given by the ethics committee of the Medical Association Westphalia-Lippe and the University of Muenster (approval number: 2021-356-f-S).

### The intervention: development of the online platform JamesAKTIV

An essential part of the ParkinsonAKTIV study is the development and use of the online platform called JamesAKTIV. Various professions, such as neurologists, physiotherapists, occupational therapists, speech and language pathologists, PD nurses, representatives of a German statutory health insurance, and IT specialists were involved in the development of JamesAKTIV. One major feature of JamesAKTIV is the digital quickcard for each patient which aims to establish guideline-based non-pharmacological therapy recommendations and to enhance structured communication between health professionals involved in care for patients with PD. The development process of quickcards is described in detail elsewhere [8].

JamesAKTIV contains the following features:Quickcards that can be filled out and shared between neurologists and therapists.A comments function for quick exchange of relevant information.A download section to access assessment forms.Individual patient accounts for therapy information and administration.A video section explaining the ParkinsonAKTIV project in detail.Educational videos for specific therapeutic interventions.

### Use of JamesAKTIV

As illustrated in Fig. 1, treating neurologists log into JamesAKTIV and create a case for the PD patient under treatment. When the treating neurologist subscribes a non-pharmacological treatment, such as physiotherapy to their patient, he or she documents this treatment on JamesAKTIV as specific as possible. After an assessment by the therapist, a final decision is established between the neurologist and the therapist. Once the patient receives personalized treatment by a therapist, the kind of therapy (e.g., backpack training for camptocormia) is again documented in the quickcard by the physiotherapist and the progress, duration and the kind of therapy can be monitored by the treating neurologist.

**Fig. 1 Fig1:**
[figure not shown]
Illustration of JamesAKTIV

### Study setting and training of staff

The intervention takes place in a specified area in the northwest of Germany (Muensterland and Osnabrueck). In this area, two multidisciplinary voluntary care networks of PD healthcare professionals exist, namely the PNM+ and the Parkinson’s Network Osnabrueck+(PNO+). Participating therapists and neurologists were recruited via these regional networks as well as from outside the networks in the region. All professionals participating in ParkinsonAKTIV are required to complete a 2-h education course on the use of JamesAKTIV. Moreover, all professionals working in ParkinsonAKTIV have had training on the use of quickcards and on diagnostics as well as treatment options in PD.

### Process evaluation

*Recruitment* Participants for the process evaluation are healthcare professionals located in the region of Muensterland, Tecklenburger Land and Osnabrueck, Germany (n = 30 neurologists and n = 150 therapists). All healthcare professionals are given access to JamesAKTIV and are invited for the quantitative process evaluation (i.e., social network analysis survey and the team effectiveness survey) via email for participation in the online survey. For the qualitative process evaluation (i.e., interviews and focus groups), a purposive sample will be drawn from all participating ParkinsonAKTIV healthcare professionals.

*Social network and team effectiveness analysis* A quantitative social network and team effectiveness analysis is performed using an online survey to analyze patterns of relationships among stakeholders within the system and to map the connection and provide insights into communication and collaboration between project partners. Another part of the online survey includes 25 questions on perceived team effectiveness, which cover aspects about psychosocial team characteristics and norms, dynamics and processes, such as communication, decision-making and potential conflicts within the team, and team outcomes [17].

*Interviews and focus groups* For semi-structured interviews, approximately, 10 – 15 healthcare professionals from ParkinsonAKTIV are approached and asked to participate in telephone interviews. The interviews aim to shed light on factors such as the acceptance of ParkinsonAKTIV (i.e., JamesAKTIV) for routine care implementation, willingness to work with JamesAKTIV, as well as its barriers and facilitators. In addition, focus groups with participating healthcare professionals are conducted to investigate interdisciplinary communication between different healthcare professionals and to gain insights into the quality of network interactions.

*Data analysis* Quantitative data gained from the social network analysis are analyzed descriptively and visualized in form of nodes and ties in a graphical network that depicts the relationships between involved healthcare professionals [11]. The relationships are grouped into five dimensions of analysis: Interconnectedness: how and where interaction occur, Centrality: number of interactions with other stakeholders, Density: ratio of actual and theoretical interactions between stakeholders, Distance: whether there are indirect or direct interactions between stakeholders, and Reachability: how many steps one stakeholder takes to reach another stakeholder.

Quantitative data from the team effectiveness evaluation is analyzed descriptively by computing mean scores of all items within one concept. Then an overall sum score from all concepts will be calculated reflecting the perceived level of team effectiveness [17].

The qualitative data collected in semi-structured interviews and focus groups, consisting of field notes and transcripts of audiotapes will be analyzed according to the principles of qualitative content analysis [10]. Subsequently, the quantitative and qualitative data from the process evaluation will be triangulated.

### Effectiveness evaluation

*Recruitment of intervention group* Recruitment of PwP takes place during face-to-face consultations by their treating neurologists where further information about ParkinsonAKTIV is provided. Until the caseload is reached, all new patients that fulfil the inclusion criteria, will be enrolled into the intervention arm. Additional information about the procedure for participation is available on the PNM+ website as well as flyers.

*Recruitment of control group* To compare the treatment of PwP in ParkinsonAKTIV with standard care, members of a nationwide support group for PD, the Deutsche Parkinson Vereinigung e. V. (dPV), are approached for study participation through their member’s journal. The dPV member pool will be approached twice for participation in the survey, once for the baseline survey and once at the end of the study.

Patients eligible for the intervention arm must fulfill the following inclusion and exclusion criteria:

*Inclusion criteria*
Primary PD according to the international classification (ICD 10 G20.x)Age of ≥ 30 yearsExisting medical treatmentPD care must be fully provided in the region Muensterland, Tecklenburger Land and the district and city of Osnabrueck

*Exclusion criteria*
Secondary PDInsufficient knowledge of the German languageIntellectually and linguistically unable to answer the questionnaires

*Data collection* For the effectiveness evaluation and the health economic evaluation, quantitative data will be collected via paper–pencil surveys among PD patients (i.e., primary outcome: health-related quality of life and secondary outcomes: patient-reported healthcare costs, see Table 1). In addition, neurologists assess disease specific measures during their face-to-face consultations (i.e., secondary outcomes: disease severity and PD symptom severity, see Table 1).

*Sample size calculation* The sample size calculation is based on the primary outcome, quality of life. According to a-priori power calculation, based on an independent t-test and an effect size of d = 0.3 [3, 11]. With an alpha of 0.05 and a two-tailed comparison of means, a sample size of 176 PwP for each group would be sufficient to achieve a power of 0.80. In total, a case number of 352 PwP is needed due to the 1:1 matching. Considering a loss to follow-up in the intervention arm (estimated at 5%) [2], a total of 185 PwP needs to be initially included. PwP in the control groups will be surveyed via dPV. One study has been identified that recruited PwP via dPV with a resulting response rate of approximately 11% [12]. Considering a similar response rate of 11% for the ParkinsonAKTIV study and dPV’s current approximately 19,000 members across Germany, the inclusion of 185 PwP in the control arm appears to be reachable.

*Primary outcome* The primary outcome is health-related quality of life, assessed using the Parkinson’s Disease Questionnaire (PDQ-39, [1]). The PDQ-39 consists of 39 questions, subdivided into eight dimensions including items on symptoms, opportunities to participate, mobility and interferences in activities of daily living. Each question can be answered with following categories: “never” (= 0 points), “rarely” (= 1 point),” sometimes” (= 2 points), “often” (= 3 points) and “always” (= 4 points). A higher score indicates a reduction in quality of life (PDQ-39, [1]).

*Secondary outcomes. * The severity of PD symptoms will be assessed using the UPDRS, which evaluates various aspects of PD [5]. This instrument includes four different categories containing Part I: Non-Motor Aspects of Experiences of Daily Living, Part II: Motor Aspects of Experiences of Daily Living, Part III: Motor Examination and Part IV: Motor Complications. The questionnaire will be conducted during an interview with the respective patient by the treating neurologist. The UPDRS total score ranges from 0 to 199 points. A higher score indicates a physical or cognitive impairment of PwP [5].

The symptom progression of PD will be assessed by the treating neurologist using the Hoehn and Yahr scale [7], which comprises eight different disease stages. A higher disease stage indicates a higher limitation due to the PD [9].

The severity of PD and activities of daily living will be assessed using the PD-specific Schwab and England Activities of Daily Living scale [14] by the treating neurologist. This scale rates the functional status of patients with PD on a scale from 0, indicating worst possible function, to 100, indicating no impairment.

Healthcare service utilization will be measured using the generic Questionnaire for Health-Related Resource Use in an Elderly Population (FIMA) [15]. It contains 28 questions that consider the patients’ utilization and healthcare costs of outpatient and inpatient treatments, medications, and other treatment procedures, such as physical therapy.

*Health economic evaluation* The health economic evaluation will be performed as a cost-effectiveness analysis considering total costs (direct and indirect costs) collected from patients via FIMA and quality of life as effect measures collected via PDQ-39. In addition, a cost analysis from a payer’s perspective will be performed using routine data from a statutory health insurance.

*Data analysis* Descriptive and associated analyses will be conducted to determine sample characteristics and provide summaries of outcome measures.

The primary and secondary outcomes will be evaluated according to the intention-to-treat principle. To test the robustness of the data, per-protocol analysis with complete cases only will be performed.

For the analysis of the primary outcome measure, PD-specific quality of life, all 39 items will be grouped into eight index scores, which then represent a percentage value between 0 and 100 (100 = many health problems). In a next step, linear models will be used to examine the difference in primary outcome between groups and will be reported as gain in quality of life within the 12-monthts observation period, with a 95% confidence interval. Sensitivity analyses will be conducted using multiple regression analysis, considering covariates such as age, gender, or duration of PD.

Secondary outcomes will be analyzed with dependent t-tests, to compare for potential differences in the intervention group within the course of the study (12 months).

Cost-effectiveness will be analyzed using an incremental cost-effectiveness ratio (ICER). The ICER measures the additional cost per unit of health gain and compares the differences between the intervention arm (specified as ‘i’ in the formula) and control arm (specified as ‘c’ in the formula) in terms of the mean total costs in the numerator and mean effects in the denominator:$${\text{ICER}} = {{\left( {{\text{costs}}_{{\text{i}}} - {\text{costs}}_{{\text{c}}} } \right)} \mathord{\left/ {\vphantom {{\left( {{\text{costs}}_{{\text{i}}} - {\text{costs}}_{{\text{i}}} } \right)} {\left( {{\text{effects}}_{{\text{i}}} - {\text{effects}}_{{\text{i}}} } \right)}}} \right. \kern-0pt} {\left( {{\text{effects}}_{{\text{i}}} - {\text{effects}}_{{\text{c}}} } \right)}}$$

To address uncertainties in the cost-effectiveness analysis, cost-effectiveness planes will be plotted based on a non-parametric bootstrapping method with 5.000 bootstrap replications. Furthermore, a cost-effectiveness acceptability curve (CEAC) will be constructed and univariate sensitivity analyses will be performed.

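### The controls are self-selected support-group members, so the comparison is with usual care among responding dPV members and is open to confounding by prior therapy and membership

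*Protocol article*

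**What the plan says.** Under Effectiveness evaluation, the paragraph on control recruitment begins "To compare the treatment of PwP in ParkinsonAKTIV with standard care, members of a nationwide support group for PD" and continues that these members "are approached for study participation through their member’s journal". The sample size paragraph confirms the single source: "PwP in the control groups will be surveyed via dPV". Table 1 labels the arm as treatment as usual.

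Intervention patients come by another route. Their treating neurologists recruit them in consultations, and until the caseload is reached "all new patients that fulfil the inclusion criteria, will be enrolled into the intervention arm". The criteria require that PD care be provided in the study region; none concerns support-group membership.

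The Introduction motivates the trial by stating that "there is a nationwide lack in non-pharmacological therapies for PwP".

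The primary analysis uses linear models for the between-group difference in 12-month gain on the PDQ-39, with no covariates named. A multiple regression follows as a sensitivity analysis, "considering covariates such as age, gender, or duration of PD". The sample size paragraph refers to 1:1 matching without naming the variables.

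Table 1 schedules the FIMA at baseline and at 12 months in both arms; the intervention-only footnote is attached only to the visit in between. The FIMA covers outpatient and inpatient care, "medications, and other treatment procedures, such as physical therapy".

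**The concern.** The arms differ in how patients enter, and that difference may be linked to the outcome. Controls belong to a patient organisation, read its journal and choose to reply. Such patients may already obtain more therapy, cope differently, or be at another stage of disease than patients whom a neurologist enrols. The article does not say which.

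Prior non-pharmacological therapy deserves particular attention because ParkinsonAKTIV works by guiding that therapy. How much a patient already receives at baseline plausibly affects both the 12-month course and the room for improvement. Physician-rated severity cannot stand in for it: by Table 1, the UPDRS, Hoehn and Yahr and Schwab and England scales are collected only in the intervention arm.

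Two things are at stake. The estimated gain could be too small or too large for reasons unrelated to the intervention, and the ICER, built on the same two arms, would inherit the error. And even an unbiased result would describe benefit over usual care in responding dPV members, which is narrower than standard care.

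**Working it through.** **1. The plan's own figure.** Inputs from the sample size paragraph: d = 0.3, two-sided alpha 0.05, power 0.80.
- Normal approximation: n = 2 × (1.960 + 0.842)² / 0.3² = 174.4, so 175 per group.
- Two-sample t-test (noncentral t): 175.4, so 176 per group, with power 0.801 at 176.

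The stated 176 reproduces. The sample size is not at fault, but it presumes an unbiased contrast.

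**2. What a selection difference would do.** The article gives no size for it, so a range b (in SD of 12-month gain) is assumed. With 176 per group, SE = √(2/176) = 0.1066. For a true-plus-spurious difference δ, the two-sided rejection probability is Φ(δ/SE − 1.960) + Φ(−δ/SE − 1.960). Set δ = b for no true effect, and δ = 0.3 − b when the shift works against the intervention.

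| Assumed shift b (SD) | False-positive rate, no true effect | Power at true d = 0.3, shift against the intervention |
|---|---|---|
| 0 | 0.050 | 0.804 |
| 0.05 | 0.076 | 0.650 |
| 0.10 | 0.155 | 0.467 |
| 0.15 | 0.291 | 0.291 |
| 0.20 | 0.467 | 0.155 |

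Check at b = 0.10: 0.10/0.1066 = 0.938, and Φ(−1.022) + Φ(−2.898) = 0.153 + 0.002 = 0.155. The noncentral t gives nearly the same power (0.648 at d = 0.25 and 0.465 at d = 0.20).

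**3. Why a membership covariate adds nothing unless membership is recorded in the intervention arm.** Write gain = a + β·arm + γ·member. Every control has member = 1, so the control mean is a + γ. Intervention members have mean a + β + γ and intervention non-members a + β. Hence β is the mean of intervention members minus the mean of controls, which is exactly the members-only contrast. If membership is not recorded, or no intervention patient is a member, β and γ cannot be separated.

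**4. Precision of a members-only contrast.** The number m of intervention patients who are members is unknown. With 176 controls, the 95% half-width is 1.96 × √(1/m + 1/176):
- m = 176: 0.21 SD
- m = 88: 0.26 SD
- m = 44: 0.33 SD

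With 44 members the half-width already exceeds the design effect of 0.3.

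**5. Is matching on baseline therapy feasible?** On the plan's figures, 0.11 × 19,000 = 2,090 possible respondents at baseline, and 2,090/185 ≈ 11 per intervention patient. That leaves room for further matching variables, although controls must also respond at the end of the study.

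**The case against.** A reader might infer that the comparator is not standard care at all, and that adjustment cannot repair it. The documents do not support this. Controls receive usual treatment, and no passage shows that dPV members get more or less therapy than other patients; the only statement on supply is the nationwide lack. The question is one of representativeness and confounding, not of a different comparator treatment. Nor is repair excluded: the article states 1:1 matching, the covariate list is open-ended, and the matching variables may stand in the full protocol. Only the three named examples can be said to miss prior therapy and membership.

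The other side can also say that the design is declared quasi-experimental, that the limitations concede the absence of an RCT, and that analysing 12-month gain largely cancels stable differences in level. This is right as far as it goes. Differing trajectories remain, and the limitations do not mention the support-group source.

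Finally, the shifts in the table are assumed and would apply to any non-randomised comparison of this size. That is correct. They show how sensitive a trial sized for d = 0.3 is, not that dPV recruitment produces such a shift.

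**Conclusion.** The point holds in a limited form. All controls are self-selected members of one nationwide support group, whereas intervention patients are enrolled by neurologists in one region without regard to membership. The trial therefore estimates the effect of ParkinsonAKTIV against usual care as received by responding dPV members, with possible confounding by prior non-pharmacological therapy and by membership. The covariates named in the article address neither, and enter only a sensitivity analysis.

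The direction and size of any bias are unknown. The 0.10 SD illustration rests on an assumed shift, 176 per group with outcome data, and a simple comparison of means. It is not an estimate of the bias in this trial. The case for change rests on the low cost of the remedy and on the mismatch between the claimed and the actual comparator.

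**What to change.** 1. **Baseline therapy use.** Include non-pharmacological therapy use, as far as the baseline FIMA records it, in the 1:1 matching and in the primary PDQ-39 and cost models. The article names only physical therapy as an example, so whether occupational and speech or swallowing therapy are captured must be checked against the questionnaire. Use baseline values only: therapy during follow-up is the pathway of the intervention, and adjusting for it would remove part of the effect. Cost: analysis-plan wording, since the FIMA is already scheduled at baseline in both arms.
2. **Membership.** Add one dPV-membership item to the intervention arm's baseline form; it can be asked retrospectively. Report the contrast of intervention members with controls, with its confidence interval, as a descriptive sensitivity analysis. The drawback is low precision, and it removes neither the self-selection through the journal nor the regional versus nationwide difference.
3. **Wording.** Describe the comparator and the conclusions as usual care among responding dPV members, and state this as a limitation. Similar results in intervention members and non-members should not be used to restore the term standard care: there are no non-member controls, so that comparison cannot show what non-members would have gained under usual care. Cost: a narrower claim.

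No extra patients or visits are needed.

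### Control arm has no stated eligibility criteria, no exclusion of the intervention region and no disease-severity scale, so the 1:1 matching cannot use disease stage

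*Protocol article*

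**What the plan says.** All places are in the Protocol article.

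- **Eligibility (Effectiveness evaluation).** The list opens with "Patients eligible for the intervention arm must fulfill the following inclusion and exclusion criteria". It covers primary PD, age, existing treatment, care within the region, and the exclusions for secondary PD, language and ability to answer. No other list is given.
- **Controls (Effectiveness evaluation, recruitment of control group).** They are "members of a nationwide support group for PD", reached through the association's journal and surveyed at baseline and at the end of the study. The article does not exclude members treated in the intervention region.
- **Severity (Study design, Table 1).** UPDRS, Hoehn and Yahr, and Schwab and England carry a footnote at every timepoint: "Only assessed in the intervention group". Demographics, PDQ-39 and FIMA at baseline and 12 months carry no such footnote.
- **Matching (sample size calculation).** "In total, a case number of 352 PwP is needed due to the 1:1 matching". The matching variables are not named.
- **Adjustment (data analysis).** The primary analysis compares groups on 12-month gain in PDQ-39 with linear models. Age, gender and PD duration are given as example covariates, for sensitivity analyses only.

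**The concern.** Without randomisation, the primary comparison depends on who may enter each arm and on what can be matched or adjusted. Here the entry routes differ. Treating neurologists enrol the intervention patients face to face against stated criteria, whereas controls volunteer through a members' journal with no stated criteria.

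The two groups could differ in disease severity. If severity is related to 12-month change in quality of life, that difference would appear as a treatment effect or hide one. The three scales that measure severity exist in one arm only. A later analysis plan could name matching variables, but it could not recover baseline stage data that were never collected in controls.

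A smaller risk is that controls treated in the region by participating professionals would dilute the contrast.

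**Working it through.** **1. The plan's own sample size.** The inputs are "based on an independent t-test and an effect size of d = 0.3", "With an alpha of 0.05 and a two-tailed comparison of means" and power 0.80. The normal approximation gives 175 per group. The exact two-sample t-test gives 175.4, rounded up to 176, with power 0.801 at that size. The stated figure, "a sample size of 176 PwP for each group", is reproduced. The point concerns comparability, not this arithmetic.

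**2. What is available in both arms at baseline.**

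| Measure | Intervention | Control |
|---|---|---|
| Demographics | yes | yes |
| PDQ-39, FIMA | yes | yes |
| PD duration | named as covariate | implied by its use in a between-group model |
| UPDRS, Hoehn and Yahr, Schwab and England | yes | no |

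The routine-data row is not footnoted either. The text, however, uses those data only for a payer-perspective cost analysis and describes no link from them to disease stage. Matching or adjustment can therefore use PDQ-39 and duration, but not stage.

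**3. Possible size of the bias.** The documents give neither an imbalance nor a correlation, so both are assumptions, and no matching or adjustment is applied.

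- Bias in outcome SD = severity imbalance (SD) × correlation of severity with the analysed outcome.
- Standard error at 176 per arm = √(2/176) = 0.1066.
- Type I error = P(Z > 1.96 − bias/0.1066) + P(Z < −1.96 − bias/0.1066).
- Power if the bias opposes a true d = 0.3 is Φ((0.3 − bias)/0.1066 − 1.96).

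| Imbalance | Correlation | Bias (SD) | Share of 0.3 | Type I error | Power if opposed |
|---|---|---|---|---|---|
| 0.2 | 0.3 | 0.06 | 20% | 0.09 | 0.62 |
| 0.5 | 0.2 | 0.10 | 33% | 0.155 | 0.47 |
| 0.5 | 0.4 | 0.20 | 67% | 0.47 | 0.15 |

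If the proxies removed half of the 0.10 to 0.20 SD (also an assumption), 0.05 to 0.10 SD would remain, with type I error of about 8 to 16%.

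**4. Controls outside the criteria (assumption).** If 10% of controls would fail the criteria and differ by 0.5 SD, the control mean shifts by 0.10 × 0.5 = 0.05 SD. Type I error is then about 7.6%.

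**5. Regional dilution (assumption).** If a fraction f of controls received the full effect, the contrast is 0.3 × (1 − f). For f = 2%, 5% and 10% this is 0.294, 0.285 and 0.27, and power is about 0.79, 0.76 and 0.72.

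**6. Room to screen.** By the article's figures, 11% of 19,000 is 2,090 responders for 185 control places (185/2,090 = 9%). Fewer will answer both surveys, but the margin is wide.

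**The case against.** The case on the other side has four parts.

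- **Proxies exist.** A reader might infer that nothing collected could reveal or correct an imbalance. The documents do not support that. PDQ-39 covers symptoms, mobility and daily activities and is taken at baseline in both arms, PD duration is a named covariate, and the covariate list is open-ended. This stands, and it limits the point to stage and severity as the three scales measure them.
- **Silence in a condensed article.** A reader might also infer that controls with secondary PD, or patients already in the intervention arm, are accepted. No sentence says so. The list contains a regional criterion that could not apply to nationwide controls, which is an ordinary reason to head it as it is, and a fuller protocol may hold control criteria. This largely stands for eligibility and double enrolment. It does not reach the severity scales, because the footnote to Table 1 positively restricts them to one arm.
- **The bias figures are assumed.** They ignore the planned matching, and because the outcome is a 12-month gain, a constant baseline difference cancels. This stands: only severity that predicts change matters, and the figures are illustrations.
- **The restriction is practical.** The scales need a neurologist's assessment, and the secondary outcomes are analysed within the intervention group only. That explains the choice, and the Perspective section acknowledges that the study is not a classical randomised trial. Neither supplies a severity measure for controls, and a patient-rated item would be feasible in a paper survey.

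**Conclusion.** The point holds in a limited form. As written, the criteria bind the intervention arm only, the control pool is nationwide with no regional exclusion, and all three severity scales are missing in controls. Matching cannot use disease stage, and even the available covariates are kept out of the primary model. Baseline PDQ-39 and PD duration allow partial correction.

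Under the assumptions shown and with no matching or adjustment, the bias runs from 0.06 SD (type I error about 9%) to 0.20 SD (about 47%), against a planned effect of 0.3. A reader might take 15 to 47% as the trial's expected false-positive rate. It is not, because the imbalance and the correlation are assumed and the planned matching would lower it. The direction of any bias is unknown. Regional dilution is probably minor (power about 0.76 with 5% fully exposed controls). The change is worth making and cheap, and the finding does not invalidate the design.

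**What to change.** 1. Add a short patient-rated stage or daily-function item and year of diagnosis to the baseline questionnaire in both arms.
2. Use these with baseline PDQ-39, age and gender in the matching and in the primary linear model, not only in sensitivity analyses.
3. Apply the diagnosis, age, treatment, language and ability criteria to controls through survey screening items. Exclude controls whose PD care is in the intervention region or who take part in ParkinsonAKTIV.
4. If the control baseline survey has already been sent, collect year of diagnosis, diagnosis type and region at follow-up, and match and adjust on baseline PDQ-39 and duration. A stage item asked at 12 months cannot stand in for baseline stage, so report its absence in controls as a limit on the conclusion.

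The cost is a slightly longer survey and a few excluded respondents, which the expected response can absorb.
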